# Efficacy study comparing a CBT-I developed for shift workers (CBT-I-S) to standard CBT-I (cognitive behavioural therapy for insomnia) on sleep onset latency, total sleep time, subjective sleep quality, and daytime sleepiness: study protocol for a parallel group randomised controlled trial with online therapy groups of seven sessions each

**DOI:** 10.1186/s13063-024-08403-3

**Published:** 2024-08-26

**Keywords:** Insomnia, Shift workers, Efficacy study, CBT-I vs. a newly developed manual, Online group therapy

## Abstract

**Background:**

Shift workers are at an increased risk of developing sleep disorders. The standard therapy recommended for sleep disorders is cognitive behavioural therapy for insomnia (CBT-I). Many of its interventions are based on a regular sleep and wake rhythm, which is difficult to apply for shift workers. We have therefore developed a new therapy manual specifically for shift workers (CBT-I-S), which should be more applicable to their needs. In particular, all interventions that require regularity have been removed, and instead, interventions that address factors that proved to be relevant to sleep in our preliminary study have been integrated. We now want to test this manual for its effectiveness.

**Methods:**

A randomised controlled trial with *N* = 142 will be conducted to compare two conditions: the newly developed therapy manual will be carried out in the experimental group, while cognitive behavioural therapy for insomnia will be employed in the standard group. Both treatments will be conducted online via MS Teams in a group setting with seven sessions each. Data will be collected at three measurement points (pre, post, 6-month follow-up) and analysed using linear mixed models. The study will investigate whether the two treatments have led to significant improvements in total sleep time, sleep onset latency, subjective sleep quality and daytime sleepiness in shift workers. It will also examine whether the new therapy manual is superior to standard therapy in shift workers and whether these effects are stable.

**Discussion:**

We assume that interventions designed to address depressive mood, anxiety, worry, rumination, dysfunctional thought patterns and attitudes towards sleep will also improve sleep. If this is indeed the case, these interventions could replace previous ones that require regularity. This could significantly improve the treatment of insomnia in shift workers.

**Trial registration:**

German Clinical Trials Registry DRKS DRKS00032086. Registered on August 16, 2023.

## Introduction

### Background and rationale {6}

The current state of research on the subject of sleep or sleep disorders and their therapy is already well advanced, see various textbooks and standard works (e.g., [1–6]). In most of these studies, however, shift workers are explicitly excluded, even though this group in particular has an increased risk of sleep disorders. Reynolds et al. [7] estimate the proportion of shift workers at 20% of all employees, of whom 20–40% could suffer from clinically relevant sleep disorders.

According to Nachreiner et al. [8], shift work leads to a desynchronization of working time with both endogenous circadian and exogenous social rhythms resulting into impairments in sleep, cognitive functions, performance, and health, but also social impairments for those affected and their social environment ([8], p. 204).

Costa [9] identified the effects of shift work on sleep as a reduction in total sleep time by 2 to 4 h, an increase in the proportion of REM and stage 2 sleep, which is perceived as less restful, and more frequent and/or earlier sleep interruptions, partly for social reasons, for example to eat with the family. According to Seibt et al. [10], this is not only due to chronobiology, but also to the more difficult sleeping conditions during the day, mainly due to brightness and higher noise levels.

Sleep disorders in shift workers are listed in DSM-5 [11, 12] under 307.45, circadian rhythm disorder, shift work type. According to Drake et al. [13], one of the following criteria is present: insomnia and/or excessive sleepiness associated with working hours that fall within the usual sleep times.

The gold standard of insomnia treatment is CBT-I (cognitive behavioural therapy for insomnia). It mainly consists of psychoeducation, and cognitive restructuring of dysfunctional assumptions about sleep as well as training subjects in sleep hygiene, sleep restriction, stimulus control, and relaxation, [7, 14]. However, because these interventions require regular sleep and wake times, they are not suitable for shiftworkers [7]. In a meta-analysis [7], 10 studies were examined in which the CBT-I was partly carried out in a slightly modified form with shift workers. In some cases, however, very specific target groups were used, such as firefighters [15] or media workers [16]. Some of these studies require caution in interpreting the results, either because of a very small sample size (e.g., *N* = 19, [16]) or because of small effects [17] or lacking a control group. Sometimes non-psychological methods were used, such as a sports programme [18]. Summarising the results of studies of CBT-I in shift workers, Reynolds et al. [7] conclude that although there is a reduction in symptoms as a result of these interventions, on average this reduction does not reach clinically significant levels. They see this as evidence that the use of standard CBT-I is not appropriate for this target group.

Referring to the studies by Booker et al. [17] and Lee et al. [19], Ito-Masui et al. [20] conclude that CBT-I adapted to shift workers is effective. In their own study [20], they conducted a blended online intervention consisting of an adapted, app-supported, clinician-guided therapy. Although the results showed statistically significant improvements, they were only partially clinically significant. In addition, they did not use a control group design, and the sample consisted almost entirely of female nurses, which raises issues about the generalisability of the results.

The current state of research on the effectiveness of CBT-I for shift workers is therefore limited or suggests that previous approaches are not sufficiently effective. A recent study [21] shows very encouraging results for a digital CBT-I adapted to shift workers, although it was only tested on a waiting list control group. Another recent study [22] differentiates between daytime and night-time insomnia and has developed corresponding treatment approaches that have also led to good effects. Here, too, only a passive control group is used.

We will therefore conduct a study that takes these points of criticism into account. The contents of the manual used in this study were derived from a literature analysis and an own preliminary study that has not yet been published. Interventions that require regularity have been replaced. Alternative appointments in parallel groups as well as missing appointments are possible. In the latter case, for compensation subjects can read the content themselves online or watch it as a video.

An exaggerated focus on disturbed sleep is a strong supporting factor of the sleep disorder, which can lead to an intention to force falling asleep and thus prevent falling asleep (attention-intention-effort pathway, [23]). The newly developed manual for shift workers (CBT-I-S) derives its therapeutic rationale from this model: The focus of attention should be shifted away from (the disturbed) sleep and, implicitly, sleep should be improved. To this end, interventions are applied to other factors influencing sleep that have been shown to be relevant in our own preliminary study: depressed mood, anxiety, worrying, rumination, dysfunctional thought patterns and attitudes towards sleep. The interventions used have their primary source in behavioural and positive psychology.

In our preliminary study, attitudes to shift work were another important factor affecting sleep. Cognitive restructuring was used to help participants develop a more positive attitude towards shift work.

Only interventions that have been tried and tested over many years are used, but only from treatment manuals for other disorders. For example: generalised anxiety [24], depression [25, 26], rumination [27], and positive psychology [28].

In addition, psychoeducational material was made available on healthy sleep, sleep disorders and their treatment [4–6, 29–31]. Information on shift work tolerance [32–34] and tips for dealing with shift work [35] were also included in the manual.

The use of these methods is not expected to cause harm to the participants. On the contrary, it is expected that these interventions will have greater positive effects on shift workers than classical CBT-I, because they can be better implemented for this target group.

The aim of the present study is to answer the following research question: Can the new insomnia therapy developed for shift workers (CBT-I-S) improve the sleep of shift workers?

### Explanation for choice of comparators {6b}

As already mentioned above, studies conducted to date using classic CBT-I methods have shown little effect on shift workers. A literature analysis and our own as yet unpublished study suggest that there are alternative factors maintaining sleep disorders in this group of people, which suggest that an alternative treatment option would be useful and more effective.

### Objectives {7}

To test these hypotheses, a newly developed insomnia treatment for shift workers (CBT-I-S) will be compared with the classical treatment of sleep disorders (CBT-I). The working hypothesis is that the experimental condition (CBT-I-S) will produce significant improvements in total sleep time, sleep onset latency, subjective sleep quality and daytime sleepiness in shift workers. These positive effects will be clearly superior to those of the standard condition (CBT-I) and will remain stable for 6 months after the end of treatment.

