### Outcomes {12}

The primary outcome is improvement in the following key sleep variables: total sleep time, sleep onset latency, subjective sleep quality and daytime sleepiness. We also want to measure the severity of the sleep disorder.

Secondary outcomes are improvements in depressive mood and anxiety, dysfunctional sleep attitudes, and cognitive and physiological arousal.

Data will be collected at three time points: before starting treatment, at its end and 6 months later as a follow-up. We will compare group means between groups and within groups at each time point. Since we will have multiple primary outcomes over multiple time points, we will adjust the α-level using a Bonferroni correction.

The magnitude of the differences, especially in the pre-post comparisons, should not only be statistically, but also clinically significant. This means, for example, that subjects no longer meet the criteria for a sleep disorder (DSM-5, [11]) after treatment.

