### Statistical methods {20 a-c}

For analysing primary and secondary outcomes, we will use linear mixed-models:

We will make within-subject comparisons of the primary and secondary outcomes at the three time points before and after treatment and at follow-up. We will also make between-subject comparisons, i.e., a comparison of the three conditions at the three time points.

Mediator and moderator analyses of the moderation and mediation of the outcomes: No hypotheses about mediators and moderators will be formulated. These analyses are purely exploratory.

We expect low attrition at the post-measurement, but somewhat higher at the follow-up measurement. Individuals who did not complete the post-measurement will be excluded. Those who did not complete only the follow-up may be included in the pre-post comparison but must be excluded from the calculations of the stability of the effects. Depending on their number, it may be necessary to analyse whether they represent a group with specific characteristics. As no post- or follow-up data is expected to be available from the dropouts, an intention-to-treat analysis is not possible. Instead, a per-protocol analysis will be conducted with all participants who were present in at least 4 sessions.

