## Discussion

### Strengths

The study design differs in many ways from other studies on shift work and sleep. First and foremost, the planned sample size of *N* = 142 will give the results more statistical power and thus significance. Due to the online implementation, the acquisition of participants does not have to be limited to the geographical area around the University of Salzburg but can be extended to the entire German-speaking area. In addition, all occupational groups with shift work are included, not just one occupational group, as is the case in many studies. This means that the results can be generalised to all shift workers.

Another strength is the design with two parallel groups: experimental and standard. The effectiveness of the new protocol can be directly compared with standard treatment. The applicability for shift workers and their acceptance can also be determined with this experimental design (drop-outs). Due to the difficulty of recruiting participants, there are several weeks between enrolment and the start of therapy for some participants. Although we do not have an explicit control group, we can still use the ISI data (pre-screening vs. pre-measurement) to check whether there has been spontaneous improvement without intervention.

The development of a specific manual can also be seen as a strength of this trail. Based on literature and the results of a preliminary study, factors that have a significant impact on the sleep of shift workers have been identified. Appropriate interventions were then selected and adapted. All interventions that had to do with regular schedules were removed in order not to jeopardise participant compliance.

However, what is innovative about this treatment manual is the implicit rationale for improving sleep. It is well known that an excessive focus on sleep disturbance can perpetuate the sleep disorder. However, most insomnia therapies focus on the disturbed sleep, thereby increasing the focus on the problem. In our manual, sleep is improved by reducing worry, anxiety, depressive rumination, etc. From the start of therapy, participants understand the key to better sleep: do not think about it and do not try to influence sleep.

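### With the control arm cancelled, within-arm pre-post change cannot show that CBT-I-S works, yet the research question and first hypothesis still rest on it

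*Protocol article*

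**What the plan says.** Trial design {8} and Protocol amendments {25} record that a sleep-diary control group was dropped because recruitment was difficult. CBT-I-S and CBT-I remain, and Trial design {8} gives superiority of CBT-I-S as the aim.

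Other sections still ask whether treatment works in absolute terms:

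- Background and rationale {6} poses a single research question, with no comparator: "Can the new insomnia therapy developed for shift workers (CBT-I-S) improve the sleep of shift workers".
- Objectives {7} puts first the hypothesis that "the experimental condition (CBT-I-S) will produce significant improvements in total sleep time, sleep onset latency, subjective sleep quality and daytime sleepiness in shift workers". Superiority over CBT-I follows as a separate sentence.
- The abstract asks "whether the two treatments have led to significant improvements in total sleep time, sleep onset latency, subjective sleep quality and daytime sleepiness", for both arms, and names superiority as a further question.
- Statistical methods {20 a-c}: "We will make within-subject comparisons of the primary and secondary outcomes at the three time points".
- Outcomes {12}: "The magnitude of the differences, especially in the pre-post comparisons, should not only be statistically, but also clinically significant".

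The Strengths part of the Discussion concedes that there is no explicit control group and adds that "we can still use the ISI data (pre-screening vs. pre-measurement) to check whether there has been spontaneous improvement without intervention".

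**The concern.** The abstract's wording is causal, but the comparison behind it is uncontrolled. Participants are enrolled because they have insomnia (Eligibility criteria {10}), know their arm (Blinding {17a-b}) and mainly report on themselves (Data collection methods {18a}). Improvement from pre to post may reflect therapy, natural course, a change of rota, expectancy or regression to the mean, and a within-arm test responds to all of these alike. The analysis set adds to the difficulty: Statistical methods {20 a-c} keeps only those who completed the post-measurement and attended at least four sessions.

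The case that matters is a non-significant between-arm result with improvement in both arms. The research question would then be open, while the hypothesis as worded could be reported as met. CBT-I cannot serve as a yardstick of known efficacy, because Explanation for choice of comparators {6b} says it has had little effect in shift workers. The Background also criticises earlier studies for having no control group and promises to take that criticism into account.

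**Working it through.** **1. What the sample size covers.** Inputs from Sample size {14}: k = 2 groups, m = 3 times, f = 0.1, correlation 0.7, alpha 0.01, within-between interaction.

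- Noncentrality: N × m × f² / (1 − r) = 142 × 3 × 0.01 / 0.3 = 14.2.
- Degrees of freedom: (k − 1)(m − 1) = 2 and (N − k)(m − 1) = 280, with sphericity.
- Power is 0.803, and N = 142 is reproduced. The powered test is the randomised group-by-time contrast.

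**2. How a within-arm test behaves with no treatment effect.** Assume a non-specific improvement of d SD in both arms, from any source. Equal allocation gives 71 per arm before attrition. The SD of a change score is √(2(1 − 0.7)) = 0.775, so the paired t noncentrality is d / 0.775 × √71, with a two-sided test at 0.01.

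| d (SD) | noncentrality | P(significant), r = 0.7 | r = 0.5 | r = 0.82 |
|---|---|---|---|---|
| 0.1 | 1.09 | 0.07 | 0.04 | 0.11 |
| 0.2 | 2.18 | 0.33 | 0.18 | 0.57 |
| 0.3 | 3.26 | 0.73 | 0.46 | 0.94 |
| 0.4 | 4.35 | 0.95 | 0.76 | 0.998 |

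The value 0.82 is the lower end of the re-test reliability that the protocol quotes for the PSQI; 0.5 is an assumption. In the between-arm test a common improvement cancels: simulated at r = 0.7, its rejection rate was 0.0096 at 0.2 SD and 0.0103 at 0.3 SD.

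**3. The ISI comparison before treatment.** Three limits follow from the text.

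- Scope: it uses the ISI, not total sleep time, sleep onset latency, subjective sleep quality or daytime sleepiness.
- Interval: several weeks, for some participants only. Participant timeline {13} has 8 weeks between t1 and t2.
- Content: nobody receives attention or expects benefit from sessions during the wait.

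A fourth limit is regression to the mean. No ISI entry cut-off is stated, so its size is an assumption. Suppose that people are selected above the population mean at screening, where the mean shift is 0.798 SD, and that nothing truly changes.

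- Expected fall from screening to pre: (1 − r) × 0.798 = 0.24 SD at r = 0.7, and 0.14 SD at r = 0.82.
- If all 142 contribute at alpha 0.05, this is significant with probability 0.97 and 0.83.
- Cut-offs from −0.5 to +1 SD at r = 0.7 give falls of 0.15 to 0.46 SD.

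**4. How much of that regression reaches the pre-post interval.** With selection at screening, the expected pre-to-post fall is (r between screening and pre − r between screening and post) × mean shift.

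- Equal correlations of 0.7: (0.7 − 0.7) × 0.798 = 0, and the within-arm test stays at 0.01.
- Decaying correlations (0.7, 0.7, 0.49): 0.21 × 0.798 = 0.17 SD, significant with probability 0.23. Cut-offs from −0.5 to +1 SD give 0.11 to 0.32 SD and probabilities of 0.08 to 0.83.

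The contribution of regression to pre-post change thus runs from nothing to substantial, and the documents do not say where this trial lies.

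**The case against.** The strongest reply is that the trial is already a superiority trial. Trial design {8} says so, Objectives {7} goes straight on to superiority, and the sample size powers that contrast and nothing else. The abstract says only that the study will investigate whether improvement occurred. No equivalence claim is made, and no rule is stated for a non-significant contrast. All of this is true, and it limits the point to the absolute-efficacy wording. It does not remove that wording: the only question posed in the Background has no comparator, and the first hypothesis is met or not by within-arm tests.

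Three stronger readings are tempting and are not supported.

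- A reader might infer that regression to the mean alone makes a within-arm test falsely significant about 73% of the time: a sample 1 SD above the population mean with r = 0.7 would regress by 0.30 SD. That places all the regression between pre and post. The protocol separates pre-screening from pre-measurement, and its single correlation of 0.7, applied throughout, gives an expected pre-post regression of zero. The sum also assumes selection on the outcome itself, whereas selection is on insomnia and the four variables come from the PSQI and ESS. In the table, 0.73 is the consequence of a 0.3 SD improvement from any source.
- A reader might infer that the ISI comparison is biased in favour of treatment. Regression between screening and pre-measurement would look like spontaneous improvement, which tells against a treatment claim.
- A reader might infer that the ISI comparison is planned as a replacement control. It is a Discussion remark, made while conceding that there is no control group, and no decision depends on it.

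**Conclusion.** The point holds for absolute-efficacy claims. With two active, unblinded, self-reported arms, significant pre-post change is not evidence that CBT-I-S or CBT-I works, and a modest non-specific improvement is enough to produce it. That illustration assumes 71 analysed per arm, alpha 0.01, r = 0.7 and a common improvement whose size the documents do not give; attrition would lower the probabilities somewhat.

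The ISI comparison cannot settle the matter in either direction. A fall may be regression rather than recovery, and the absence of a fall says nothing about the four named variables or about 8 weeks of attention and expectancy.

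The randomised contrast is untouched. A positive result there would show that CBT-I-S does better than CBT-I. Reading it as improvement over no treatment would still need the assumption that CBT-I does not worsen sleep in this group.

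**What to change.** - **Abstract, Objectives {7} and Statistical methods {20 a-c}:** make the randomised CBT-I-S versus CBT-I contrast the only confirmatory basis for efficacy claims. Report within-arm change as estimates with confidence intervals and no causal wording.
- **Background and rationale {6}:** restate the question as whether CBT-I-S improves sleep more than CBT-I in shift workers.
- **Discussion, Strengths:** label the ISI waiting-period comparison as descriptive, and name its limits: ISI only, unfixed interval, some participants, regression after selection.
- **Statistical methods {20 a-c}:** add that within-arm improvement beside a non-significant between-arm result does not show that either treatment works. Correct the leftover reference there to three conditions.

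The cost is wording and the loss of an uncontrolled efficacy claim. N = 142 and the randomised comparison do not change.

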### Trial design {8}

The trial will be conducted in two parallel groups with controlled randomised allocation of the same number of subjects per group. The aim is to prove the superiority of the newly developed therapy (CBT-I-S) over standard therapy (CBT-I). Originally, an active control group was planned to keep a sleep diary for the same time period (8 weeks). Unfortunately, due to difficulties in recruiting subjects, this group had to be cancelled.

